## 5. STUDY END POINTS

### 5.1 Primary End Point(s)

#### **Safety:**

- Determine AEs and SAEs associated with NO-impregnated catheters
- Proportion of patients (%) who prematurely discontinued the study due to AEs or SAEs

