#### **Tolerability:**

- Proportion of patients (%) who prematurely discontinued the study due to AEs or SAEs associated with NO-impregnated catheter

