#### 7.5.1 Criteria for Treatment Discontinuation

- AEs that are suspected to be related to NO-impregnated catheters, according to physician discretion

- Blood pressure and heart rate above or below the 20% of the normal ranges for the patient baseline

A patient whose treatment was discontinued for any reason should complete all study assessment including the follow up visits.

Concomitant medication (i.e. antibiotics) given during the study will not be a reason for treatment early discontinuation.

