### **7.5.2 Criteria for Early Study Withdrawal**

A patient may withdraw or be withdrawn from the study for the following reasons:

- 1) Patient withdrew consent.
- 2) Protocol violation/ non-compliance.
- 3) Loss to follow-up/failure to return.
- 4) Patient with difficulty in insertion of catheter during surgery.
- 5) In cases which require catheter replacement.
- 6) Serious adverse event

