#### **Per Protocol Cohort:**

The Per-Protocol cohort includes all patients in the ITT cohort who complete the study (completed study treatment) in compliance with the protocol and have no major protocol violations.

For the ITT cohort, the Last Observation Carried Forward (LOCF) approach will be applied, when deemed appropriate, to account for missing data at or prior to study termination.

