#### **Tolerability Assessments**

Tolerability analysis will be based on the number (%) of patients who failed to complete the study, the number (%) of patients who failed to complete the study due to AEs. Time to withdrawal will be presented by Kaplan-Meier curves. Significance testing of time to withdrawal will be done using Cox's proportional hazards model.

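### Tolerability is counted as leaving the study, yet a patient whose catheter is removed for a non-serious related adverse event is told to stay in it

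*Protocol*

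**What the plan says.** The protocol has one tolerability endpoint, in the Synopsis and in Section 5.1: "Proportion of patients (%) who prematurely discontinued the study due to AEs or SAEs associated with NO-impregnated catheter". The second safety endpoint uses the same construction without the link to the catheter: "Proportion of patients (%) who prematurely discontinued the study due to AEs or SAEs". Section 13.4 (Tolerability Assessments) follows suit: "Tolerability analysis will be based on the number (%) of patients who failed to complete the study", overall and due to AEs, with Kaplan-Meier curves and a Cox model for time to withdrawal.

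Section 7.5 then keeps two lists.

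- Section 7.5.1 gives the criteria for stopping treatment. The first is "AEs that are suspected to be related to NO-impregnated catheters, according to physician discretion". It adds: "A patient whose treatment was discontinued for any reason should complete all study assessment including the follow up visits".
- Section 7.5.2 gives the reasons for withdrawal from the study. Two of the six bear on this point: "Serious adverse event" and "In cases which require catheter replacement". The other four are withdrawn consent, protocol violation, loss to follow-up and difficult insertion at surgery.

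Other sections use the two ideas loosely. Section 13.3 defines the Per Protocol cohort as those who "complete the study (completed study treatment) in compliance with the protocol". Section 6.1 ties completion per protocol to completed study treatment, but dates it 30-45 days after catheterization. The text of Section 7.5 speaks of discontinuing the study under a heading about stopping treatment. Section 8.6 deals with premature catheter removal, and with withdrawal because of an AE, under study discontinuation.

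**The concern.** For an indwelling catheter, the direct sign of poor tolerability is that it has to come out because of an AE. The endpoint, the second safety endpoint and the Section 13.4 analyses all count something else, namely departure from the study. Section 7.5.1 sends a patient with a suspected related AE down the treatment-stop route and asks the site to keep him in follow-up. A site that follows that instruction well can then report a low tolerability event rate although catheters were removed.

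At stake is the headline proportion for one of the two primary objectives in a study of 12 patients. The AE data would not be lost, but the figure labelled tolerability could miss the cases it is meant to show, or could differ between two analysts who rely on different sections.

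**Working it through.** The protocol states no expected rate, power or effect size for this endpoint, so there is no figure to reproduce. The check follows one patient through the text and then sizes the effect.

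**Step 1: plain reading.** Take a man in the NO-impregnated group with local irritation, non-serious and suspected to be related. His catheter is removed under Section 7.5.1 and he attends Visit 5 as that section directs. None of the six reasons in Section 7.5.2 applies. He has not discontinued the study, so he is not an event for:

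- the tolerability endpoint (5.1);
- the second safety endpoint (5.1);
- the number failing to complete the study (13.4);
- time to withdrawal (13.4), where he contributes no event.

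**Step 2: the same man under other sections.** Section 13.3 glosses study completion as completed treatment, Section 6.1 links the two, and Section 8.6 treats premature catheter removal under study discontinuation. On that reading he is an event. The protocol does not say which reading governs.

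**Step 3: does the gap fall on plausible events?** Section 11.4.2 and Appendix 5 anticipate lower blood pressure, bleeding or longer bleeding time, erection and local irritation. Appendix 5 ends by saying that life-threatening, hospitalization-prolonging, disabling or fatal events are not expected. The intolerance that the protocol itself foresees is therefore mostly non-serious, which is what Section 7.5.2 leaves out.

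**Step 4: size.** Input: n = 6 in the NO-impregnated group (Section 6.1). One patient is 1/6 = 16.7 percentage points. The exact (Clopper-Pearson) 95% limits for x/n are the 2.5% quantile of Beta(x, n-x+1) and the 97.5% quantile of Beta(x+1, n-x). For x = 0 the lower limit is 0 and the upper limit is 1 - 0.025^(1/6) = 45.9%. The counts below are assumed, because the protocol gives none.

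| Assumed removals for a non-serious related AE, all followed up | Endpoint, plain reading | Endpoint counting the removals |
|---|---|---|
| 1 | 0/6 = 0% (0 to 45.9%) | 1/6 = 16.7% (0.4 to 64.1%) |
| 2 | 0/6 = 0% (0 to 45.9%) | 2/6 = 33.3% (4.3 to 77.7%) |
| 3 | 0/6 = 0% (0 to 45.9%) | 3/6 = 50% (11.8 to 88.2%) |

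**Step 5: chance that the gap matters at all.** If each treated patient has probability p of such a removal, the chance of at least one among six is 1 - (1-p)^6. For assumed p:

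- 10%: 1 - 0.9^6 = 46.9%
- 20%: 1 - 0.8^6 = 73.8%
- 30%: 1 - 0.7^6 = 88.2%

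**The case against.** The strongest reply is that attending follow-up is not the same as completing the study. Section 7.5 asks that patients who discontinue early still be followed on the regular visit schedule, so in this protocol a man can be both a discontinuer and in follow-up. Together with Sections 6.1, 8.6 and 13.3, this allows an early removal for an AE to be counted. That stands, and it means that 0/6 is one reading and not the only one. It does not rescue the endpoint, because the result then turns on which section the analyst follows. Section 8.6 also foresees withdrawal for an AE without requiring it to be serious, but it refers back to Section 7.5 for the criteria.

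Three stronger conclusions might be inferred, and the documents do not support them.

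- *That the rate is driven to zero whatever the catheter does.* A related serious AE, or a related AE that requires catheter replacement, can lead to withdrawal under Section 7.5.2 and then counts.
- *That catheter intolerance would go unseen.* AEs associated with the catheter are themselves a primary safety endpoint. Section 13 plans separate tables for them, and Section 13.4 tabulates AEs by action taken and by relationship to the catheter.
- *That the planned group comparison is empty, because a control patient cannot have an event tied to an NO-impregnated catheter.* The hypothesis (3.2) and primary objectives (4.1) concern the NO-impregnated catheter alone. The test wording in Section 13 is generic, and the discontinuation proportions that it names (for any reason, and due to any AE or SAE) are defined in both groups.

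**Conclusion.** The point holds in a limited form. On the plain wording of Sections 5.1, 7.5.1, 7.5.2 and 13.4, removal of the catheter for a non-serious related AE, in a patient who is then followed up, is not a tolerability event. Other sections allow the opposite reading, so the primary proportion is either wrong for its purpose or undetermined.

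Each affected patient moves the result by 16.7 percentage points. The intervals are wide on either reading, and the study claims no power, so no formal conclusion is overturned. What fails is the meaning of the reported figure. The illustrated counts and rates are assumptions. The finding itself rests only on the wording.

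It should be corrected in the protocol, because the protocol itself fixes the primary endpoint and Section 20.2 has the analysis performed as the protocol defines it.

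**What to change.** Define the tolerability event in the Synopsis, Section 5.1 and Section 13.4 as removal of the study catheter that the investigator attributes to an AE or SAE. Report it as (a) AEs of any causality and (b) AEs judged related to the study catheter, with the same definition in both groups. Then:

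- report withdrawal from the study as a separate item, for any reason and due to AEs;
- make the Kaplan-Meier and Cox variable in Section 13.4 the time from insertion to AE-driven catheter removal;
- reconcile Sections 6.1, 7.5, 8.6 and 13.3 with this wording, so that stopping treatment and leaving the study are distinct throughout.

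The definition should rest on the attributed reason and not on a planned removal date, since the protocol gives only a window (day 7-21±7) and no date per patient. No clinical rule for when a catheter is removed needs to change.

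The cost is protocol wording. Placement and removal dates (18.2), AE details and causality (11.2), action taken (12) and reasons for discontinuation (8.6) are already to be recorded. The downside for the sponsor is that the reported rate may look less favourable.

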### 5.2 Observational

- Proportion of patients (%) who prematurely discontinued the study for any reason
- Measure and compare the biofilm formation on the surface of NO-impregnated versus non-impregnated Foley catheters after indwelling for 7-21±7 days
- Measure and compare bacteriuria (by urine culture) for NO-impregnated versus non-impregnated Foley catheters prior to insertion, on catheter insertion day, every day during hospitalization, on catheter removal day, and 30-45 days after catheterization
- Compare occurrences of clinically significant UTIs following catheterization with NO-impregnated and non-impregnated Foley catheters
- Record different species of bacterial contaminations

### 5.3 Safety and Tolerability

All measurements will be done continuously to avoid exceeding allowed range of the up mentioned parameters.

#### 5.3.1 Vital Sign Measurements

Full physicals examination will be performed by a study physician on each visit and every day during hospitalization (visit 2). Abbreviated physical examination (vital signs) by a study coordinator or by the medical staff will be done on each visit and during hospitalization 3 times per day.

Cardiovascular status will be determined by monitoring heart rate and blood pressure. Values will be recorded every 8 hours (3 times per day).

\* Vital signs measurement includes the followings parameters: body temperature, blood pressure and heart rate.

### **5.3.2 Laboratory Tests: Blood & Urine**

#### **Blood:**

- Complete Blood Cells Count (CBC).
- Blood biochemistry (electrolytes, renal and liver function tests).
- Coagulation tests (PT, aPTT, INR).

#### **Urine:**

- Urine sterile specimen for culture will be obtained prior to insertion, on catheter insertion day, every day during hospitalization, on catheter removal day, and 30-45 days after catheterization
- Urine for biochemical tests including nitrate concentration

## 6. STUDY DESIGN

### 6.1 Overview and Plan

This is a Prospective, Phase I, Open-label Case Series, Single-Center study.

A total of 12 patients, over the age of 18, undergoing radical prostatectomy will be enrolled. Screening data will be reviewed to determine patients' eligibility and informed consents will be obtained.

Patients who meet all inclusion criteria and none of the exclusion criteria will be enrolled.

6 patients will be allocated to receive NO-impregnated Foley catheters (treatment) followed by 6 patients allocated to receive non-NO-impregnated Foley catheters (control).

A patient will receive catheter up to  $21 \pm 7$  days of study treatment. A patient is considered as completed the study "per protocol", once study treatment was completed: 30-45 days after catheterization.

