| 
Statistical Considerations:
 | 
All measured variables and derived parameters will be listed individually and, if appropriate, tabulated by descriptive statistics. For categorical variables summary tables will be provided giving sample size, absolute and relative frequency and 95% Confidence Interval (CI) for proportions by study group.
 
For continuous variables summary tables will be provided giving sample size, arithmetic mean, standard deviation, coefficient of variation (if appropriate), median, minimum and maximum, percentiles and 95% CI for means of variables by study group.
 
Statistical Methods:
 
The study objective is to demonstrate a safety profile and tolerability. All adverse events will be coded according to coding dictionaries (MedDRA version 16.1 or higher) and presented in tables by System Organ Class (SOC) and Preferred Term (PT). Drug-related adverse events will be presented as well.
 
95% CI will be calculated for the proportion of patients who prematurely discontinued the study for any reason and due to any AE or SAE.
 
Chi-square test or Fisher's Exact test (as is appropriate) will be used for analyzing the difference in proportions between the study groups. The Paired T-test or Signed rank test for two means (as is appropriate) will be applied for analyzing changes in continuous parameters within study group.
 
The two-sample T-test or Non-parametric Wilcoxon-Mann-Whitney Rank sum test for independent samples (as is appropriate) will be applied for analyzing differences in continuous parameters between the study groups.
 
All tests will be two-tailed, and a p-value of 5% or less will be considered statistically significant.
 
The data will be analyzed using the SAS ® version 9.1 (SAS Institute, Cary North Carolina).
 |

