## **7. STUDY POPULATION**

### **7.1 Number of Patients**

A total of 12 patients, over the age of 18 undergoing radical prostatectomy will be enrolled.

The study is not expected to show statistical significance or statistical power, but to demonstrate a safety and tolerability profile.

6 patients will be catheterized with NO-impregnated Foley catheters followed by 6 patients catheterized with non-NO-impregnated Foley catheters.

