#### **Observational Assessment**

95% CI will be calculated for the proportion of patients with catheter-related urinary tract infections at any time point.

Chi-square test or Fisher's Exact test (as appropriate) will be used for analyzing the difference in the above proportions between the study groups.

The Paired T-test or Signed Rank test for two means (paired observations; as is appropriate) will be applied for testing the statistical significance of the changes from baseline to any post-baseline measurement in biofilm formation on the surface and bacteriuria within study group.

The two-sample T-test or Non-parametric Wilcoxon-Mann-Whitney Rank sum test for independent samples (as appropriate) will be applied for testing the statistical significance of the differences in the above parameters between the study groups.

All tests will be two-tailed, and a *p-value* of 5% or less will be considered statistically significant.

The data will be analyzed using the SAS ® version 9.1 (SAS Institute, Cary North Carolina).

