### 13.1 Sample Size Rationale

Total of 12 patients.

The planned sample size of 12 patients for the Phase I trial took under consideration the possibility of a 10% drop, as detailed in section 7.5. The planned sample size considered adequate by the sponsor and investigators for this study. The study is not expected to show statistical significance or statistical power, only demonstrate a safety profile.

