### 13.2 Randomization

N/A

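### All six NO-catheter patients come before all six controls, so arm and enrollment period cannot be separated, yet the protocol plans 5% between-arm tests and a Cox significance test

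*Protocol*

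**What the plan says.** The allocation order is given four times: twice in the synopsis, in section 6.1 ("6 patients will be allocated to receive NO-impregnated Foley catheters (treatment) followed by 6 patients allocated to receive non-NO-impregnated Foley catheters (control") and in section 7.1 ("6 patients will be catheterized with NO-impregnated Foley catheters followed by 6 patients catheterized with non-NO-impregnated Foley catheters"). The study is open label at one center. Sections 8.2 and 13.2 both answer N/A under randomization.

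The objectives and endpoints include comparing biofilm, bacteriuria and clinically significant UTIs between the two catheters. For these, section 13 (Observational Assessment) plans tests of proportions: "Chi-square test or Fisher's Exact test (as appropriate) will be used for analyzing the difference in the above proportions between the study groups". Continuous measures get a two-sample t-test or a rank-sum test. Section 13 (Safety and Tolerability) also tests proportions between groups. The decision rule, in the synopsis and again in section 13, is: "All tests will be two-tailed, and a p-value of 5% or less will be considered statistically significant". Under Tolerability Assessments in section 13.4, Kaplan-Meier curves are followed by: "Significance testing of time to withdrawal will be done using Cox's proportional hazards model".

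Section 13.1 states: "The study is not expected to show statistical significance or statistical power, only demonstrate a safety profile". The synopsis and section 7.1 say much the same. The protocol neither adjusts for the sequential enrollment nor limits inference because of it.

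**The concern.** Every NO patient is in the first half of enrollment and every control in the second. Anything that shifts between the two halves becomes part of the arm difference. Standard care is not fixed in detail, antibiotics are allowed, and catheters are impregnated in a separate process, so practice, antibiotic use, catheter lot or assay batch could differ by period. The next assignment is also known before consent, and synopsis exclusion criterion 5 leaves room for physician opinion, so patient selection could follow the arm.

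The statement about significance and power does not deal with this. Low power concerns missed differences, whereas a period shift can produce a difference where the device has no effect. A p-value below 5% for biofilm or bacteriuria would be significant under the protocol's own rule but could not be attributed to nitric oxide.

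The Cox test raises a second problem: with 12 patients and few withdrawals there is little for the model to use.

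**Working it through.** **The protocol's own figure.** The sample size is 12 (section 13.1: "The planned sample size of 12 patients for the Phase I trial"). It has no effect size, power or event count behind it, so there is nothing to reproduce. The usable inputs are 6 per arm, two-sided 5%, and a possible 10% drop.

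**Share of a drift that enters the arm difference.** Assume an outcome changes linearly from patient 1 to patient 12.
- Mean position of the NO patients: (1 + … + 6)/6 = 3.5
- Mean position of the controls: (7 + … + 12)/6 = 9.5
- Difference 9.5 − 3.5 = 6, over a range of 12 − 1 = 11: 6/11 = 0.545

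A total drift of 1 SD would thus give a bias of 0.55 SD. As a separate illustration, suppose a step shift between the two blocks and no device effect. The two-sample t-test then rejects in 13% of simulated trials for a 0.5 SD shift, 35% for 1 SD and 65% for 1.5 SD. The documents give no drift, so all these sizes are assumptions.

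**Cox model.** Section 13.4 names no covariate; arm is inferred from the two-group design. Let d be the withdrawal probability, equal in both arms. The arm hazard ratio has no finite estimate if at least one arm has no withdrawals:

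P = 1 − (1 − (1 − d)^6)²

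At d = 0.10:
- Expected withdrawals: 12 × 0.10 = 1.2
- 0.9^6 = 0.531
- No withdrawals in either arm: 0.531² = 28.2%. The ratio is undefined.
- Withdrawals in one arm only: 2 × 0.531 × 0.469 = 49.8%. The ratio is zero or infinite.
- Sum: 78.0% (simulation, 40,000 trials: 78.0%)

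| d (both arms) | No finite hazard ratio |
|---|---|
| 5% | 93% |
| 10% | 78% |
| 15% | 61% |
| 20% | 46% |
| 30% | 22% |

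The figure falls below one half at about d = 18.5%. With unequal rates it is 65% at 10% v 20% and 59% at 10% v 30%.

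A score (log-rank) test needs only one event, so at 10% it can be computed in 100 − 28 = 72% of trials. Under equal rates it rejects in about 0.1% of simulated trials, far below the nominal 5%. For 80% power at a hazard ratio of 3, the Schoenfeld formula asks for 27 events, more than the 12 patients. Even 12 withdrawals would give only 48%.

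**Fisher's exact test, 6 v 6.**
- 4/6 v 0/6: p = 0.061
- 5/6 v 0/6: p = 0.015

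With no events in one arm, the other needs at least five of six. By comparison, the exact 95% confidence interval is 0 to 45.9% for 0/6 and 0.4 to 64.1% for 1/6.

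**The case against.** The best defense is that this is a declared phase I case series. Its hypothesis concerns the safety and tolerability of the NO catheter, the comparative outcomes are labelled observational, and significance and power are disclaimed. Confidence intervals by group and Kaplan-Meier curves are already planned. Much of this stands: there is no hidden power claim, and the Fisher thresholds only put figures on a weakness that the protocol admits. It does not explain why the same document sets a significance rule and a Cox significance test, and it leaves the bias from the sequence untouched.

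A reader might infer stronger points that the documents do not support:

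- **That the Cox test will usually be impossible.** The 78% concerns a finite hazard ratio. Section 13.4 plans significance testing, and a score test fails only when nobody withdraws (28% at a 10% rate). The 78% also depends on the rate. Section 13.1 speaks only of a possible 10%, and the withdrawal criteria in section 7.5.2 (difficult insertion, catheter replacement, a serious adverse event) could raise it.
- **That practice, antibiotics, lots and assays do change with arm.** They could, but no section says that they do, and the study is short (about 6 months in all, at one center).
- **That treating NO patients first brings no safety gain.** The protocol gives no reason for the order. This is first use in humans, and section 7.5.3 stops the study for re-evaluation after a death, so an early problem could spare controls from enrolling. Against that, no review is placed between the two blocks.
- **That the trial must be randomized.** For a 12-patient first-in-human series this is a design choice.

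**Conclusion.** The point holds as a conflict within the protocol and an unstated limit on what the trial can show. The complete overlap of arm and enrollment period follows directly from sections 6.1, 7.1, 8.2 and 13.2 and needs no assumption. The 5% rule and the Cox significance test contradict the statement in section 13.1.

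The sizes are conditional. The 55% share assumes linear drift. The 78% assumes 10% withdrawal in both arms and arm as the covariate, and ranges from 93% to 22% for withdrawal of 5% to 30%. At the protocol's own rate, the Cox test would usually yield no finite hazard ratio and, where a score test can be computed, would have almost no chance of detecting a difference. The descriptive safety account of the six NO patients is not affected.

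**What to change.** In the synopsis and section 13:

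1. Delete the Cox significance test. Keep the Kaplan-Meier curves and list the individual withdrawal times.
2. Delete the 5% significance rule for between-arm comparisons. Report arm differences with exact confidence intervals, labelled descriptive only.
3. State that arm comparisons of biofilm, bacteriuria, UTI and adverse events are confounded with enrollment period and cannot be attributed to nitric oxide.

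These are changes of wording. They need no extra patients, visits or data. As a protocol amendment they need the approvals in section 14.4.

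**Option.** Randomize the same 12 patients 1:1 from a concealed list, opened only after eligibility is confirmed. This would remove the systematic overlap of arm and period. It costs a larger amendment, both catheter types on hand at each operation, and a later sixth NO patient; it also gives up whatever purpose the device-first order serves. Small fixed blocks in an open-label trial reduce predictability but do not remove it. Randomizing does not cure the sparse events, so the Cox test should go in either case.
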